### Outcomes

Assessments will be performed before the treatments, at 4 weeks after treatments, and at 8 weeks after treatments.

#### Primary outcomes

Patients undergo three-dimensional gait analysis and fNIRS detection during the walking under three tasks statuses.

Three types of walking task designs: (1) Single gait test: requiring patients to walk in a natural gait within the three-dimensional gait test area without cognitive tasks; (2) Dual task test I: requiring patients to count loudly while walking, increasing the count from 1; (3) Dual task test II: requiring patients to report loudly the names of animals while walking, and try to say as many animal names as possible.

##### Three-dimensional gait analysis

Objective gait quantification under the three different tasks is performed using three-dimensional motion-capture system. British Vicon Optical Motion Capture System (consisting of 6 high-speed infrared cameras) is used to assess the spatiotemporal variables of gait performance, and data are processed by the Vicon Polygon data analysis software. Vicon’s Nexus system detects gait parameters and kinematic parameters, including step length, stride, pace, step width, step frequency, single/double stand phase, turning (time and number of steps required for turning), swing phase.

##### fNIRS

The fNIRS data will be collected using a LIGHTNIRS research-grade portable near-infrared brain function imaging system (manufactured by Shimadzu Corporation, Japan). This system is equipped with 8 light sources and 8 detectors, configured to form 22 channels. It emits light at three wavelengths (780, 805, and 830 nm) and records the raw intensity signals at a sampling frequency of 13.33 Hz. During the gait tasks, we will ensure that the subject’s head is as stationary as possible to minimize movement artifacts. The system will record changes in HbO2 levels in the prefrontal cortex during different walking tasks. The data will be analyzed at three time points: before treatment, after 4 weeks, and after 8 weeks of treatment.

#### Secondary outcomes

##### Mini-mental state examination (MMSE)

MMSE is used to measure cognitive impairment and includes six aspects: time orientation, location orientation, immediate and delayed memory, attention and calculation ability, language, and visual space (18). MMSE is a 30-point questionnaire, and 1 point is assigned for each correct answer. Testing scores are closely related to education level, and the standard for dividing the normal threshold is >17 points for patients with illiteracy, >20 points for patients with primary school, >22 points for patients with secondary school, and > 23 points for patients with junior college (18).

##### Montreal cognitive assessment (MoCA)

MoCA includes eight cognitive domains: attention and concentration, executive function, memory, language, visual space, abstract thinking, computation, and orientation (19). Total score of this scale is 30 points, and patients with a score of ≥26 points are defined as normal (19).

##### Barthel index (BI)

BI is used to assess the physical function status of patients, and the total score ranges from 0 to 100 (20). The functional impairment is divided into mild (> 60 points), moderate (40–60 points), and severe level (≤ 40 points).

#### Adverse events

All patients will be requested to report adverse events, and acupuncturists will record adverse events in detail including date, severity, duration, and measures taken by researchers. The causes are analyzed and causal relationship with the treatment is assessed. Adverse reactions occurring during the trial include dizziness needles, bending needles, and broken needles during acupuncture, adverse physiological reactions during gait walking, and hair heating during the use of fNIRS.

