## Introduction

Alzheimer’s disease (AD) is a degenerative disorder of the central nervous system, which is characterized by cognitive impairment and behavioral impairment (1). AD is the most common cause of dementia, and accounts for 60–80% of the cases globally (2). It is estimated that the number of AD patients will exceed 30 million, and about 50% of people over 80 years old will suffer from AD in China by 2050 (3). AD patients not only lose working ability, sociability, self-care ability, and quality of life, but also bring a heavy burden to their families (4).

Non-pharmacological interventions have been reported as the important choices for AD patients (1). Among the non-pharmacological interventions, 78% of patients in China select acupuncture-related treatments (5). Acupuncture has been used clinically in China for many years because of small wound, mild pain, and high security (6, 7). Studies have reported the efficacy of acupuncture in the improvement of cognitive impairment for AD patients (1, 8). Cognitive impairments are often associated with motor disorders, including bradykinesia, rigidity, balance, and gait disorders, which increases the risk of falls (9). The gait of AD patients has gradually attracted attention, and elderly people with AD are twice as likely to suffer from traumatic falls as their peers without AD (10). The effect of acupuncture treatment on the gait performance has been reported in neurodegenerative diseases and brain diseases (11, 12). Pereira et al. found that there were statistically significant differences between acupuncture group and sham-acupuncture group in the gait speed, gait cadence, left–right step length of patients with Parkinson disease, indicating that acupuncture could improve gait in Parkinson disease patients (11). Lou et al. found that step length, gait speed, step frequency, and ground reaction force impulse of stroke patients significantly increased after the acupuncture treatment, indicating that acupuncture could help to improve the gait performance of stroke patients (12). However, the effect of acupuncture on the gait performance has not been reported in AD patients.

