### Study population

#### Diagnosis criteria

The diagnostic criteria of AD from Western medicine will be determined according to The National Institute on Aging-Alzheimer’s Association (NIA-AA) (15): (1) cognitive decline that affects daily life and includes damages to two or more cognitive domains; (2) early and most significant cognitive impairment belonging to the past phenotype or non-forgetting phenotype (language disorder, visual spatial disorder, or executive dysfunction); (3) excluding vascular dementia, Lewy body dementia, frontotemporal dementia, primary progressive semantic aphasia, and other active neurological disorders; (4) with biomarkers of brain amyloid-beta (Aβ) protein deposition.

The diagnostic criteria of AD from traditional Chinese medicine will be determined according to Chinese Internal Medicine (16): (1) onset symptoms, main symptoms: decreased ability to remember recent and distant events, cognitive decline (such as ability to judge people, objects, time, location, calculation ability, spatial recognition, language, etc.); accompanying symptoms: character changes such as withdrawn personality, indifferent expression, selfishness and narrowness, stubbornness, irrational euphoria, easy to get excited or angry, decreased understanding, and personality changes such as lack of morality and ethics, and lack of shame; (2) characteristics of onset: hidden onset, slow progression, and long course of disease; (3) syndrome of insufficient marrow-sea: memory loss, loss of recognition and calculation, dull expression, lifeless eyes, low and timid voice or silence all day; slow movement, tinnitus and deafness, withered auricula, hair loss and tooth shaking; red and thin tongue, white tongue moss, and weak pulse.

The dementia stage will be determined using Clinical Dementia Rating (CDR), which assesses cognitive and functional decline from 6 domains: memory, orientation, judgment and problem solving, community affairs, home and hobbies, and personal care (17). The dementia is divided into none (CDR = 0), questionable (CDR = 0.5), mild (CDR = 1), moderate (CDR = 2), and severe level (CDR = 3) (17).

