#### Inclusion criteria

The inclusion criteria are as follows:

Aged 40–85 years old;Meeting the mentioned-above diagnostic criteria from traditional Chinese medicine and Western medicine;With mild to moderate dementia (CDR = 0.5, 1.0, or 2.0 points);Hachinski Ischemic Scale (HIS) ≤ 4 points;Hamilton Depression Rating Scale (HAMD) < 20 points;Without severe bone and joint diseases and able to walk independently;Able to conduct vision and hearing tests;Volunteering to participate in this trial and signing an informed consent form.

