### Follow-up

Both the experimental and control groups will undergo continuous treatment for 8 weeks. Assessments of relevant indicators will be conducted by designated personnel at three time points: before treatment, after 4 weeks, and after 8 weeks of treatment. Additionally, participants will be followed up within 1 month after completing the treatment. Each assessment will take place in a private room, allowing family members to participate in the evaluation process.

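### Adverse events are reported by patients selected for memory impairment and recorded by acupuncturists, so events away from staff are likely to be under-counted, possibly unequally between arms

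*Protocol article*

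**What the plan says.** The Adverse events section names a reporter and a recorder. On reporting: "All patients will be requested to report adverse events". On recording: "acupuncturists will record adverse events in detail including date, severity, duration, and measures taken by researchers". It then promises an analysis of causes and of the relation to treatment. Its examples are all tied to trial procedures: "Adverse reactions occurring during the trial include dizziness needles, bending needles, and broken needles during acupuncture", followed by physical reactions in the walking test and warming of the hair under fNIRS.

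The Inclusion criteria require "Meeting the mentioned-above diagnostic criteria from traditional Chinese medicine and Western medicine". Among the main symptoms in the traditional Chinese medicine set, the first is "decreased ability to remember recent and distant events". The stage admitted is "With mild to moderate dementia (CDR = 0.5, 1.0, or 2.0 points").

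The Introduction links gait disorder with cognitive impairment to falls and adds that "elderly people with AD are twice as likely to suffer from traumatic falls as their peers without AD".

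Two other provisions bear on the point. Cognitive rehabilitation, given in both arms, runs five times a week for 8 weeks. The Follow-up section describes the assessments as "allowing family members to participate in the evaluation process" and adds a contact within a month after treatment ends.

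**The concern.** A reporting route that depends on the patient's memory suits this population poorly. Staff can see a bent needle or a reaction during the walking test. They cannot see a fall at home, and the route the article sets out does not ask about one. Yet the trial aims to change how these patients walk, and falls are the harm that its own Introduction attaches to gait.

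Two things are at stake. First, a low recorded rate may be taken as a low true rate. Second, the stated recorders are the people who deliver the experimental treatment. Control patients have no treatment sessions with them, so the chance that an event is written down may depend on the arm. The promised causality assessment also needs events to have been captured in the first place.

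**Working it through.** **Provisions side by side**

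- *Who reports:* the patient, on request. No caregiver, record check or scheduled questioning is named for adverse events.
- *Who is the patient:* both diagnostic sets must be met. The Western set alone also allows a presentation led by language, visuospatial or executive problems. The memory requirement comes from the traditional Chinese medicine set, which lists memory decline among the main symptoms and again under the syndrome.
- *Who records:* acupuncturists, for all patients. Under Intervention, only the acupuncture arm receives acupuncture.
- *Which contacts exist:* sessions five times a week in both arms, assessments at weeks 4 and 8, and one contact after treatment. The article links none of them to adverse-event questions. After week 8 the frequent sessions stop.

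**The plan's own figures**

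The article states no adverse-event rate, so there is none to reproduce. The only figure used from it is the planned 54 patients per arm. That follows from its sample-size inputs (43 / (1 - 0.20) = 53.75, rounded up to 54) and is not in dispute here.

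**Illustration (all event and capture rates are assumptions)**

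Formula: recorded rate = true rate × share of events captured.

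*Absolute rates.* With an assumed true rate of 20% and capture between 0.3 and 0.8, the recorded rate lies between 0.20 × 0.3 = 6% and 0.20 × 0.8 = 16%.

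*No events recorded in one arm of 54.* The one-sided 95% upper limit is 1 - 0.05^(1/54) = 5.4% at full capture. If only half of events are captured, the limit for the true rate is about 5.4% / 0.5 = 10.8%.

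*Comparison between arms:*

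| True rate, control / acupuncture | Capture, control / acupuncture | Recorded, control / acupuncture | Risk difference (points) | Risk ratio |
|---|---|---|---|---|
| 10% / 10% | 50% / 50% | 5% / 5% | 0 | 1.0 |
| 10% / 10% | 50% / 80% | 5% / 8% | +3 | 1.6 |
| 10% / 10% | 80% / 50% | 8% / 5% | -3 | 0.625 |
| 10% / 15% | 100% / 100% | 10% / 15% | +5 | 1.5 |
| 10% / 15% | 50% / 50% | 5% / 7.5% | +2.5 | 1.5 |
| 10% / 15% | 50% / 80% | 5% / 12% | +7 | 2.4 |
| 10% / 15% | 80% / 50% | 8% / 7.5% | -0.5 | 0.94 |

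Equal under-capture lowers both rates and halves the risk difference in the fifth row, but leaves the risk ratio unchanged. Unequal capture can create, inflate or hide a difference, depending on which arm is captured better.

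**The case against.** The strongest reply is that reporting is not recall over long gaps. Both arms have one-on-one training five times a week, so during treatment staff meet each patient every few days and may notice an injury or a changed walk. Family members may take part in assessments, and nothing stops them from raising an event. Entry includes CDR 0.5 and 1 as well as 2, and impaired recall is not absent recall. The listed reactions are introduced as examples and do not restrict what may be reported. Finally, this is a condensed article, and the full protocol or CRF may contain prompts or informant questions.

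Much of this stands, and it rules out four stronger readings that a reader might infer:

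- *That acupuncture will look too safe.* The document does not support a direction for the comparison. Equal under-capture leaves the risk ratio alone, and recording by acupuncturists could mean better capture in their own arm, which would make acupuncture look worse. No formal safety conclusion is planned either.
- *That a difference in falls could not be seen.* Under equal capture the risk difference shrinks but does not vanish.
- *That family members attend every assessment.* The Follow-up section gives permission only.
- *That no informant is used at all.* The article's silence does not show this.

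The part that fails is the claim that nothing is fixed badly. The article does set out who reports and who records, and it does not connect the frequent sessions or the family's presence to that route.

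**Conclusion.** The point holds as a weakness in a stated rule. Patient report recorded by acupuncturists is a poor route in a trial that selects for memory impairment. Under-counting of events away from staff is likely, though not demonstrated, so absolute rates may be too low. Capture may also differ between arms, with an error of unknown direction. The size cannot be derived from the document, and the percentages above only show how the mechanism works under assumed rates. The conclusion rests on the article's stated route being the one used; informant questioning laid down in the full protocol would weaken it.

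**What to change.** In the Adverse events section, add a short structured adverse-event question, worded and scheduled identically in both arms:

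- Put it to the patient and, where available, a family member or caregiver at weeks 4 and 8 and at the post-treatment contact.
- Include one fixed item on falls since the last contact.
- Have it asked by existing trial staff who are neither the treating acupuncturist nor the blinded efficacy evaluator, so that capture does not depend on the arm and the evaluator's blinding is kept.
- Report adverse events and falls by arm.

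Acupuncturists can continue to record the needle events that they see. The cost is about one CRF page and a few minutes per contact, at contacts already planned. Patients without an informant will still rely on self-report and should be flagged as such. The change concerns data collection only and alters no treatment.

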### Blinding

Due to the particularity of acupuncture, it is difficult to blind clinical operators and participants. Patients will be informed of the treatment method after receiving grouping information. The efficacy evaluator will be blind. Cognitive function evaluation will be conducted by the researcher who is unaware of the allocation. Liver and kidney function and electrocardiogram testing will be completed by the inspector who is unaware of the allocation. The statistician will be blind when performing statistical analysis. The researchers, clinical operators, and efficacy evaluator are independent.

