### Intervention

The control group will receive conventional drug therapy and cognitive rehabilitation therapy. The acupuncture group will receive acupuncture treatment based on the control group. The acupuncture operators are professional acupuncturists who have worked for more than 2 years.

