##### Cognitive rehabilitation therapy

The cognitive training system (JZ-RZ-1020, Extreme Medical Technology, Hangzhou, China) will be used to help develop personalized rehabilitation plans for one-on-one training based on the cognitive function of each patient. The trainings include memory, hand eye reinforcement, attention, reaction. Patients are treated for 30 min each time and 5 times a week for 8 weeks.

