#### Acupuncture group

The acupuncture treatment will be conducted based on the control group.

Acupoints: Baihui (GV20), Sishencong (EX-HN1), Fengchi (GB20), Taixi (KI3), Zusanli (ST36), Sanyinjiao (SP6), Neiguan (PC6), and Shenmen (HT7) (Supplementary material 2).

GV20 and EX-HN1: Patients are placed in a suitable position, and local disinfection is performed with 75% alcohol. The 28^#^ stainless-steel needles (Huatuo, Suzhou Medical Instruments Factory, China) will be used in this study with a size of 1.5 inches. When entering the needle, the needle body forms an angle of about 30° with the scalp. The needle tip points forward and enters the GV20, and needle in the EX-HN1 pointed to the GV20 direction. The needle is quickly pierced into the scalp, with a horizontal needling of 0.5 to 0.8 inches. When the resistance under the needle decreases, the needle body is inserted along the subgaleal area in the direction of the acupoint line. When patients achieve the Deqi sensation that characterized by a soreness, numbness, and distention, twisting and replenishing method is used and lasts for 2 min (200 times/min). The needle is left for 6 h, and the twisting and replenishing method is performed every 2 h during the needle retention period. The operation lasts for 1 min each time, for 3 times, until the needle is pulled out.

GB20, KI3, ST36, SP6, PC6, and HT7: Patients are placed in a supine position, followed by acupoints determination and disinfection, and 1.5-inch or 2-inch needle is used. The needle, toward the tip of the nose, is obliquely inserted into GB20 with a depth of 0.8–1.2 inches, and twirling reinforcing-reducing method is used. The needle is obliquely inserted upwards into PC6 with a depth of 1–2 inches, and directly inserted into HT7 with a depth of 0.3–0.5 inches and into KI3 with a depth of 0.5–0.8 inches. The needle, slightly tilted toward the tibia, is directly inserted into ST36 with a depth of 1–2 inches. SP6 is directly needled with a depth of 1–1.5 inches. The twisting and replenishing method is used for limb acupoints, and needles are left for 30 min. The operation when starting the needle is standard to prevent bleeding and hematoma.

To ensure the uniformity of operations, the acupuncture sequence for EX-HN1 is front, back, left, and right. The acupoints on both sides are first punctured on the left side, and then on the right side. Acupuncture treatment is performed once a day (five times a week) and lasts for 8 weeks.

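### Acupuncturists are the only named recorders of adverse events, and only one arm has scheduled sessions with them, so harms would be ascertained unequally.

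*Protocol article*

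**What the plan says.** The Adverse events section of the protocol article sets the rule: "All patients will be requested to report adverse events, and acupuncturists will record adverse events in detail". The record is to cover date, severity, duration and measures taken, and causality is then assessed. The section goes on to give examples: "Adverse reactions occurring during the trial include dizziness needles, bending needles, and broken needles during acupuncture", followed by reactions during the gait test and heating during fNIRS.

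The Intervention section defines the arms. "The control group will receive conventional drug therapy and cognitive rehabilitation therapy", and "The acupuncture group will receive acupuncture treatment based on the control group". There is no sham. On frequency, the Acupuncture group section says "Acupuncture treatment is performed once a day (five times a week) and lasts for 8 weeks", and for the scalp points "The needle is left for 6 h, and the twisting and replenishing method is performed every 2 h during the needle retention period". Cognitive rehabilitation, which both arms receive, is equally frequent: "Patients are treated for 30 min each time and 5 times a week for 8 weeks".

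The Blinding section concedes that "it is difficult to blind clinical operators and participants" and says that operators are independent of the researchers and of the efficacy evaluator, who is blind. The Follow-up section has designated personnel assess both arms before treatment and at weeks 4 and 8, with a further contact within a month after treatment. Table 1 has no row for adverse events.

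**The concern.** Reporting is asked of all patients, but writing the reports down is given to staff who treat one arm only. An acupuncture patient meets a recorder at every treatment visit and stays under that person's care for hours. A control patient has no scheduled meeting with one. Minor or transient events are easily lost when nobody asks, so the control arm could be under-recorded relative to the acupuncture arm.

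The recorder also knows the allocation and delivers the treatment whose harms are being recorded, which could pull the other way if operators play down events they cause. The plan protects its efficacy ratings from knowledge of allocation but leaves the harms record exposed to it. The causality assessment would rest on the same records.

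At stake is the safety description of the trial. A spurious excess of harm or a spurious reassurance could each arise with no true difference between arms, and events that were never elicited cannot be recovered at analysis.

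**Working it through.** The plan gives no adverse-event figure to reproduce. The check is a comparison of sections followed by an illustration.

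**Scheduled contacts over 8 weeks**

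| Contact | Acupuncture arm | Control arm | Named as recorder |
|---|---|---|---|
| Acupuncture sessions (Acupuncture group) | 5 × 8 = 40 | 0 | Yes |
| Cognitive training sessions (Cognitive rehabilitation therapy) | 5 × 8 = 40 | 5 × 8 = 40 | No |
| On-treatment assessments, weeks 4 and 8 (Follow-up) | 2 | 2 | No |
| Contact within a month after treatment (Follow-up) | 1 | 1 | No |

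The contacts shared by both arms are balanced. The only contact with the named recorder is not.

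**Illustration on assumed figures.** Only the 54 per arm comes from the documents (Sample size estimation). Assume:
- the same true risk *p* of at least one event in both arms, with *p* = 10%, 20% or 30%;
- capture of 90% in the acupuncture arm;
- capture *c* of 70%, 50% or 30% in the control arm.

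Recorded risks are 0.9*p* and *cp*, so the apparent risk ratio is 0.9/*c*, whatever *p* is: 0.9/0.7 = 1.29, 0.9/0.5 = 1.8 and 0.9/0.3 = 3.0. Expected recorded counts are 54 × 0.9*p* against 54 × *cp*. The chance of p < 0.05 comes from exact enumeration of the two binomial distributions.

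| *p* | *c* | Expected, acupuncture vs control | Uncorrected chi-square | Fisher |
|---|---|---|---|---|
| 10% | 70% | 4.9 vs 3.8 | 6% | 2% |
| 10% | 50% | 4.9 vs 2.7 | 12% | 5% |
| 10% | 30% | 4.9 vs 1.6 | 24% | 11% |
| 20% | 70% | 9.7 vs 7.6 | 9% | 5% |
| 20% | 50% | 9.7 vs 5.4 | 22% | 14% |
| 20% | 30% | 9.7 vs 3.2 | 49% | 36% |
| 30% | 70% | 14.6 vs 11.3 | 11% | 7% |
| 30% | 50% | 14.6 vs 8.1 | 34% | 25% |
| 30% | 30% | 14.6 vs 4.9 | 70% | 60% |

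With equal 90% capture in both arms, chi-square rejects in about 5% and Fisher in 2% to 3%. The excess over those values is due to capture alone. The range runs from almost nothing to severe, and the documents give no basis for choosing a row. If operators under-record their own events, the direction reverses.

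**The case against.** The strongest reply is that this is a condensed article. All patients are asked to report, nothing forbids an acupuncturist from taking a control patient's report, and both arms have frequent contact with other staff. The Data management and quality control section adds a uniform case report form, completed by researchers and checked by a monitoring team. The sentence might therefore describe the acupuncture arm's procedure only, with control-arm recording set out elsewhere.

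Part of this stands. It would go too far to say that control patients never meet an acupuncturist; the text shows only that no contact is scheduled. But the article does not leave the recorder open. It names one, for events reported by all patients. A uniform form and monitoring check that forms are completed as planned; they do not assign anyone to ask control patients.

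Three stronger readings are tempting and unsupported:

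- **That a chi-square safety comparison is fixed.** Chi-square is the general rule for categorical data under Statistical analysis. Adverse events are not mentioned there and are not among the primary or secondary outcomes.
- **That only needle, gait-test and fNIRS events will be recorded.** The list is introduced as what reactions include. It does not exclude falls or drug effects.
- **That a particular false-positive rate follows.** Any single figure rests on assumed risks and capture rates.

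**Conclusion.** The point holds in a limited form. Followed as written, the recording rule gives unequal ascertainment of harms: 40 scheduled sessions with the unblinded recorder in one arm and none in the other. Any counts by arm, tested or merely tabulated, could differ for that reason alone. This conclusion rests on the stated regimens and on reading the recorder sentence as applying to all patients, which is its plain sense. Size and net direction remain unknown. The primary and secondary outcomes and the sample size are not affected. The rule should be changed before data collection, since no analysis can restore events that were not elicited.

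**What to change.** Give the recording of general adverse events to staff whom both arms already see. Either the cognitive-rehabilitation therapist or the designated assessors at weeks 4 and 8 and at the post-treatment follow-up would serve. They should ask every patient the same non-leading question, with a specific item on falls, at the same times, and enter the answers on the same case report form. If the blinded assessors do this, the question should come after the efficacy ratings, because answers may reveal allocation.

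Acupuncturists should record needle-specific events on a separate page. These would be described for the acupuncture arm only and kept out of any between-arm comparison, since they cannot occur in controls.

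The cost is protocol and form wording and a small amount of staff time at contacts already planned. The sample size does not change. Some asymmetry will remain: patients know their treatment, and the acupuncture arm still has more clinical contact. The trial report should say so.
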